# **Introduction**

The Community Development Project financed by the World Bank in Togo is implementing an approach to social welfare via two social safety net (SSN) programs, namely: (a) school meals for approximately 38,000 primary school students in the country’s most vulnerable areas, and (b) labor-intensive public works employing 25,000 young people in rural areas. In light of these programs’ successes, and in an attempt to sustain Togo’s ongoing efforts to realize the establishment of social welfare policies that address the needs of the most vulnerable populations, the World Bank and the Togolese government opted to renew funding for the PDC, while adding an element dedicated to a conditional cash transfer pilot project (PDCPlus). This pilot project, in partnership with the Togolese government (MASSN and MDBAJEJ) and UNICEF, will launch in June 2014 in five districts in the Kara and Savanes regions and will last for 30 months. It will coordinate with a childhood malnutrition healthcare program carried out by regional health services in these districts and financed by UNICEF, and will incorporate certain flexible conditionalities (encouraged, not mandatory). The project is aimed at pregnant women and mothers of children under 24 months old; its objectives are to encourage behavior conducive to the protection and well-being of beneficiary children, and to improve their nutrition and health.

The current protocol concerns the impact evaluation of the cash transfer pilot project. It attempts to determine the effectiveness of cash transfers in conjunction with the program dedicated to preventing and treating acute malnutrition through changes observed in the following indicators: nutritional status, diet, child welfare, care, and morbidity; the protocol also aims to assess the program’s impact pathways. This evaluation will be conducted by the Joint Research Unit Nutripass of IRD, in scientific partnership with the PHND (Poverty, Health, and Nutrition Division) of IFPRI.

A process evaluation and program cost analysis are also planned, but these are addressed in other protocol documents.

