Given the considerations outlined above, the duration of the program (30 months), and logistical considerations about sample sizes at particular age ranges, we propose sampling children six to 29 months of age at endline (two years after the baseline). Sampling the six-to-29-month age range is a compromise that takes into account a minimum program exposure of 12 months and first exposure to the program no later than six months of age. These criteria are based on the assumption that the main program intervention of cash transfers will begin immediately following the baseline survey and continue for 30 months, although at the time of the endline survey no child would have been exposed to the program for more than 24 months. Any delay in the start of cash transfers will have an impact on the age range of children to be sampled.

Table 1 below illustrates the age of first exposure, and duration of exposure of children of different ages, assuming a period of 24 months between baseline and endline surveys, and an immediate start to the cash transfer program after the baseline survey:

Table 1 : Program exposure of sample age range at endline

| **Age (mo)  at Endline** | **Age (mo) at First Exposure to Program** | **Age (mo)at Last Exposure to Program** | **Total Program Exposure (mo)** |
| --- | --- | --- | --- |
| 0 | -6 | 0 | 6 |
| 6 | -6 | 6 | 12 |
| 12 | -6 | 12 | 18 |
| 18 | -6 | 18 | 24 |
| 24 | 0 | 24 | 24 |
| 30 | 6 | 24 | 18 |
| 36 | 12 | 24 | 12 |
| 42 | 18 | 24 | 6 |
| 48 | 24 | 24 | 0 |
| 54 | N/A | N/A | 0 |
| 60 | N/A | N/A | 0 |

Extensive information will be collected at the levels of villages, households, mothers, and children, in order to:

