### **3.2.2. Sampling**

The study will be of an experimental type, involving randomization at the village level. Five districts in the Savanes and Kara regions, representing a total of 273 villages, were initially selected using the criteria of poverty and malnutrition rates. Random distribution between the control group and the intervention group was stratified by district, and the village selection was proportional to each district’s population in order to reach a desired 4,800 children in the control group aged 24 months or younger. At the end of this process, 81 villages in total were placed in the intervention group. In order to balance the sampling at cluster level, 81 villages were selected from the remaining 192 and placed in the control group.

All pregnant women (from the third month of pregnancy onward) and children under 2 years old living in the selected villages will be enrolled in the program. The baseline and endline surveys will sample, respectively, children aged six to 59 months old and six to 30 months old who live in these 162 villages, as well as their mothers.

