 depending on whether we are interested in, respectively, a quantitative variable or a qualitative binary variable, in the following form:

**
[figure not shown]
=
[figure not shown]
+
[figure not shown]
*phase+
[figure not shown]
*group+
[figure not shown]
*phase*group**

Here, “phase” represents the survey (coded 0 for baseline and 1 for endline) and “group” represents the randomization group (coded 0 for the control group and 1 for the intervention group).
[figure not shown]
 is the effect of the phase (the difference between baseline and endline surveys),
[figure not shown]
 represents the difference between individuals in the intervention group and the control group, and
[figure not shown]
 represents the intervention’s effect on the intervention group or the difference-in-differences estimator.

**Using birthweight as an example, the table and figure below illustrate the significance of the various coefficients described above:**

[figure not shown]

[figure not shown]

Initially, analyses will be carried out via intention-to-treat (ITT) analysis; mother-child pairs (“CME”) and households will be analyzed within their initial randomization group, whether or not they have actually received cash transfers. A later set of analyses will use per-protocol analysis (or treatment-on-the-treated [TOT]); only mother-child pairs who have actually received cash transfers will remain in the intervention group, and those pairs who have not will be excluded from further analyses.

Pre-specified outcomes to be analyzed are as follows:

Primary outcomes:

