**Health pathway**

- Child’s health: morbidity over the previous 15 days, child’s health since birth as perceived by the mother, vaccinations, vitamin A supplementation, deworming, regular medical follow-ups and age at last medical follow-up, health-seeking behavior (children taken to a health center if sick)
- Maternal health: antenatal and postnatal care (number of consultations, stage of pregnancy at first antenatal visit, malaria IPT, tetanus vaccines, iron supplementation) delivery in health facilities, delivery assisted by a skilled birth attendant, birth weight and LBW of newborns

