# **V. Calendar**

A calendar detailing the preparation and execution of the initial survey is included below. Currently, the survey is scheduled to begin in May 2014 and is projected to last about 45 days.

The final survey will take place 24 months after the first, in May 2016.

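### Antenatal, delivery and birth-weight outcomes carry no restriction by birth date, although roughly 21-29% of the endline children were born at or before the start of transfers

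*Protocol*

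**What the plan says.** Section 3.2.1 sets the endline sample: "we propose sampling children six to 29 months of age at endline (two years after the baseline". It defends this range by a minimum length of exposure and by first exposure no later than six months after birth. Table 1 then gives first exposure by age at endline, assuming 24 months between surveys and an "immediate start to the cash transfer program after the baseline survey". Its entries for age at first exposure are -6 months for a child aged 18 months at endline, 0 for one aged 24 months, and 6 for one aged 30 months.

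Section 3.2.2 words the age ranges differently, as "respectively, children aged six to 59 months old and six to 30 months old who live in these 162 villages".

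The health pathway in section 3.2.6 lists antenatal and postnatal care together with "delivery in health facilities, delivery assisted by a skilled birth attendant, birth weight and LBW of newborns", and names no sub-population. The same section describes a single phase-by-group model for the indicators of interest and introduces its illustration with "Using birthweight as an example, the table and figure below illustrate the significance of the various coefficients described above". For the main analysis, mother-child pairs and households "will be analyzed within their initial randomization group, whether or not they have actually received cash transfers". A later analysis drops intervention-group pairs that received no transfer.

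On dates, the Introduction says the pilot "will launch in June 2014 in five districts in the Kara and Savanes regions and will last for 30 months", and the Calendar says "The final survey will take place 24 months after the first, in May 2016".

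**The concern.** The age window was chosen for growth and feeding, where a child first exposed at birth or some months later can still benefit. Antenatal care, place and attendance of delivery, birth weight and LBW are settled by the time the child is born. A child born before transfers began adds nothing to the effect on these outcomes, only weight to the average.

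Followed as written, the plan pools births that the program could have influenced with births that it could not. The estimate is pulled toward zero and power falls. A null result on maternal care or birth weight could then reflect the age window and not the program. These outcomes matter to the program's logic: women are enrolled from the third month of pregnancy, and four antenatal consultations are one of the encouraged conditions (sections 2.3.1 and 2.3.3).

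The treatment-on-the-treated analysis does not help. It selects on receipt of transfers, so a pair first paid after the birth stays in.

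**Working it through.** **1. Reproducing Table 1.** With 24 months between the start of transfers and endline:
- first exposure = max(-6, age - 24)
- last exposure = min(age, 24)
- total = last - first

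All nine numeric rows (ages 0 to 48 months) reproduce exactly. For example, age 18 gives -6/18/24, age 24 gives 0/24/24 and age 30 gives 6/24/18.

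**2. Share born at or before the start.** The assumption is that these outcomes refer to the pregnancy and birth of the sampled child. Ages are counted in completed months, so 6-29 months is 24 bands.
- Equal numbers per band, immediate start: ages 24-29 are 6/24 = 25.0%.
- Planned counts in section 3.2.3 (802 per group aged 6-23 months, 1,020 aged 6-29 months, both stated for baseline): (1,020 - 802)/1,020 = 218/1,020 = 21.4%.
- June 2014 launch and May 2016 endline, so 23 months of transfers: ages 23-29 are 7/24 = 29.2%.
- Section 3.2.2's upper limit of 30 months, if read as 25 bands: 7/25 = 28%. Combined with the 23-month interval this becomes 8/25 = 32%. That figure stacks two readings and is left outside the headline range.

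**3. Coverage during pregnancy.** Table 1's earliest exposure is six months before birth. With an immediate start:
- ages 6-17 months: covered from about the third month of pregnancy, 12/24 = 50%
- ages 18-23 months: covered for only part of that period, 6/24 = 25%
- ages 24-29 months: not covered in pregnancy, 6/24 = 25%

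**4. Dilution for delivery and birth-weight outcomes.** Let e be the unexposable share. The expected effect is (1 - e) times the mean effect among exposable births. This is exact for differences in means or proportions and approximate on the log-odds scale. The sample needed for equal power rises by 1/(1 - e)². Dropping the unexposable births multiplies the test statistic by √(1 - e)/(1 - e) = 1/√(1 - e), ignoring clustering.

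For power, assume that a full effect in the whole sample would have 90% power at two-sided 0.05 (the protocol does not state sidedness), so z = 1.960 + 1.282 = 3.242:
- unrestricted power = Φ((1 - e) × 3.242 - 1.960)
- restricted power = Φ(√(1 - e) × 3.242 - 1.960)

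| e | Effect retained | Sample inflation | Test statistic after restriction | Power unrestricted | Power restricted |
|---|---|---|---|---|---|
| 21.4% | 79% | 1.62 | ×1.13 | 72% | 82% |
| 25.0% | 75% | 1.78 | ×1.15 | 68% | 80% |
| 29.2% | 71% | 1.99 | ×1.19 | 63% | 78% |

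**5. Antenatal outcomes.** The documents do not say how much of the effect a partly covered pregnancy would show. Let that fraction be p. The pooled effect is 0.50 + 0.25p of the full effect: 50% at p = 0, 62.5% at p = 0.5, 75% at p = 1. Keeping only ages 6-17 months multiplies the test statistic by √0.5/(0.50 + 0.25p): 1.41, 1.13 and 0.94 respectively. The break-even is p = (0.707 - 0.50)/0.25 ≈ 0.83. Restriction therefore always removes the dilution, but it gains power only if partly covered pregnancies show less than about 83% of the full effect.

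**The case against.** The strongest objection is that the protocol never says, for these outcomes by name, that every child aged 6-29 months is analysed. The outcome list gives names without denominators. Intention to treat fixes the arm and not each indicator's denominator. The table and figure of the birth-weight example are not visible, and an analysis plan not shown here could add a restriction. This stands as a caution on wording. It does not remove the point, because the protocol itself fixes the outcomes, the general model and the population, and offers birth weight as the illustration, all without reference to birth date. What is proposed is a better analysis of data already collected, not a missing detail.

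It can also be said that the protocol does consider exposure timing, and warns that a delayed start would alter the ages to be sampled. That reasoning is directed at feeding and nutritional outcomes. Moving the sampled range does not say which births count for delivery or birth weight. Nor is this ordinary intention-to-treat dilution from low uptake, since no degree of uptake could have influenced these births.

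A reader might infer more than the documents support:
- Table 1 does not itself show that a quarter of children are unexposed. It gives exposure by age and no age distribution, and the 25% needs the uniform-age assumption.
- 75% is not an upper bound on the retained effect; the planned counts give 79%.
- Counting 13 of 24 bands as covered from about month three would treat the 18-month band as exactly 18.0 months while treating the 24-month band as a whole month. Consistent banding gives 12.
- Postnatal care sits in the same list but is not settled at birth. It can still respond for births shortly before launch.

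**Conclusion.** The point holds as an inexpensive improvement to the analysis of intermediate outcomes. About 21-29% of endline children could not show an effect on delivery, birth weight or LBW, so those effects are expected to appear at about 71-79% of their size among exposable births. Antenatal outcomes are diluted further, by an amount that depends on how partly covered pregnancies respond. The range rests on the age distribution, on the actual start of transfers, and on these outcomes referring to the sampled child's birth. The power figures also rest on the assumed 90% starting point.

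It would be wrong to infer that the randomised comparison is compromised, that a false positive effect could arise, or that the primary outcome is touched. The bias is toward no effect, the full-sample estimate remains valid for the children surveyed, and HAZ is not concerned.

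**What to change.** State the birth cohort for each outcome family:

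- **Delivery place, skilled attendance, birth weight, LBW:** main analysis in children under 24 months at endline, with the same age window at baseline and in both arms.
- **Antenatal outcomes:** main analysis in children under 18 months, applied in the same way.
- **Delayed start:** shift both cuts using one common or district-level program start date applied to both arms. With 23 months from launch to endline, the cuts become 23 and 17 months. A village-specific first-transfer date should not be used, because control villages have none and the rule would select births differently by arm.
- **Postnatal care:** leave it outside the strict cut, or treat it separately.
- **Supporting analyses:** report the full 6-29 month sample as a sensitivity analysis, and ages 24-29 months as a check where no effect is expected. That check will be imprecise, with about 218 children per group by the planned counts.

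Sections 3.2.1 and 3.2.2 should also be brought to one statement of the surveyed ages, so that the cuts are unambiguous.

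The cost is a sentence per outcome family and no new data. The analysed sample falls by about 21-29% for delivery and birth-weight outcomes, which is outweighed by removing the dilution (test statistic about 15% higher at a 25% share, ignoring clustering). By the planned counts, 802 per group remain, the number on which the study was first sized. For antenatal outcomes about half the sample is lost. The gain there is mainly in interpretability, since the gain in power is conditional.

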**Hygiene pathway (through spot checks)**

- Child’s hygiene: cleanliness of hands, face, hair and clothes
- Mother’s hygiene: cleanliness of hands, face, hair and clothes
- Yard’s sanitary conditions: animal feces, waste

**Knowledge and awareness pathway**

- Mother’s knowledge of nutrition, health, and hygiene

**Women empowerment pathway**

- Decision-making power
- Intimate partner violence (IPV)

**Child welfare pathway**

- Child fostering
- Enrollment in school
- Birth registration

# **IV. Ethics**

Overall, the evaluation will conform to the ethical standards common to this kind of work; the present protocol will be submitted to the Togolese national ethics committee for approval.

The following standards will be applied:

-Information and request for authorization from community authorities: UNICEF and the CDP will be charged with alerting relevant authorities (mayor, prefect) to the establishment of this cash transfer program and its evaluation. In each study village, IRD teams will visit village authorities (village and religious leaders) in order to present the study’s objectives and implementation and obtain their authorization.

-Free and informed participation: each household or individual participating in one of the above activities will receive detailed written information about the study’s objectives and implementation, with regard to their participation in it. These elements will also be explained during initial sensitization, either in the respondent’s native tongue or a language they understand easily, and questions may be asked at this time if desired. Consent will be obtained via the head of household (or their spouse, if absent), though any members of the household reserve the right to opt out of the survey without any negative consequences for themselves, their families, or their loved ones. A household or individual may also revoke consent at any time, postpone interviewers’ visits, or refuse to answer any questionnaire items, all without needing any justification.

-Risks: the evaluation does not represent any risks to participants, as it consists simply of questionnaires administered by interviewers and some painless, non-invasive anthropometric measurements.

-Confidentiality and anonymity: the confidentiality of responses will be guaranteed at every step of the survey, from data gathering to the final analysis and publishing of results; questionnaires will be processed anonymously and no computerized results will contain any identifying information.

-Expected benefits: these primarily concern participating mothers and children, as cash transfers will hopefully better their everyday lives (through improved nutritional intake, better medical monitoring, etc.) and lead to a reduction in morbidity and an enhanced nutritional status. The benefits will also concern other children in the household via flexible conditionalities (schooling of eligible children’s siblings, avoiding foster care); additionally, these children should profit from their mothers’ knowledge of nutrition, health, and child welfare, accrued through monthly sensitization sessions. The entire household could potentially benefit from the fact that the cash may be freely spent; notably, household food security is expected to improve. Finally, benefits will also pertain to the entire local community, as the study should lead to improvements in the interventions themselves or those of the same type; in a broader sense, the study will allow national and international decision-makers to be better informed about the potential effects, whether beneficial or detrimental, of this program.

-Comparison group: program effects will be evaluated through a comparison with a group of women (and their children) who will not receive cash transfers, but who nonetheless will benefit from UNICEF activities comprising detection and treatment of severe acute malnutrition.

-Emergencies: all participants, whether from the beneficiary group or the control group, are eligible for medical treatment in the event of emergencies observed during visits; medical costs will be covered in cases of severe health problems, as treatment of malnutrition is already provided for as part of the ICCM-Nut.

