### **3.2.4. Survey organization**

Both the baseline and endline surveys will take place during home visits conducted by qualified interviewers, duly selected and trained for this specific study. They will be directly supervised and evaluated by experienced agents. The questionnaire will be administered confidentially, ideally over a period of 90 to 120 minutes, and will be followed by 10 to 15 minutes of anthropometric measuring conducted under standardized conditions. The questionnaires will be digital and loaded onto tablet PCs (via the Open Data Kit [ODK] system), except for the questionnaires regarding village characteristics and household composition.

Four interviewer-pathfinder duos will be charged with notifying and sensitizing the villages and households involved in the study. They will explain the study objectives, inform subjects of their next interviews, and obtain the necessary prior approval. These duos will also be in charge of completing the questionnaire concerning the village and will take a census of all members of households involved in the study to complete the household composition questionnaire. The duos will therefore pass from village to village a few days before the interviewers visit.

Approximately 30 interviewers will be recruited and trained on the questionnaires and anthropometric measurements. Five supervisors will be hired, each responsible for a team of six people. In order to guarantee the quality of the data, supervisors will initially accompany interviewers in person (thus making sure they are correctly administering the questionnaires, correctly entering collected data, etc.). A dedicated server will receive regular transmissions of data, so study directors can remotely monitor both the figures and work progress.

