**Mother’s characteristics:** This component consists of mothers’ civil statuses, education levels, and revenue sources.

**Schedule and child care:** Mothers’ schedules will be examined, as they can directly influence dietary practices and child care. The time mothers spend taking care of their children (meals, games, healthcare) will be observed with particular interest.

**Mother’s status, autonomy, and decision-making power:** This component will assess women’s household autonomy (particularly with regard to finances), the treatment they endure within the household (abuse, insults, anxieties, etc.), their involvement in sensitization meetings and social/community networks, and their decision-making power relative to issues of diet, health, education, family planning, and children’s rights within their households.

**Use of health services and attendance at informational sessions:** This component will take into account pregnancy history, household situations during the course of pregnancy (reduced work, improved diet, etc.), the number of pre- and post-natal consultations, birth setting and external help received, and mothers’ involvement in training sessions on children’s health, diet, and rights.

**Mother’s knowledge, attitudes, and practices (“CAP”):** The program aims to improve mothers’ knowledge bases in order to impact their dietary practices and their conduct relating to the caretaking, hygiene, nutrition, and rights of their children. After adjusting for certain variables such as education and socioeconomic levels, changes in the CAP between the baseline and endline surveys will be examined to evaluate the program’s impact pathways. The CAP questionnaires will be adapted to the content of the monthly information sessions planned in the project.

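### Mothers are asked at home about abuse and partner violence, but the Ethics section takes consent via the head of household and states that the evaluation carries no risk

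*Protocol*

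**What the plan says.** Section 3.2.6 (Data analysis) lists "Intimate partner violence (IPV" among the pre-specified intermediate outcomes, under the women's empowerment pathway. Section 3.2.5 says that the component on the mother's status and autonomy covers "the treatment they endure within the household (abuse, insults, anxieties, etc".

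Section 3.2.4 fixes the setting: "Both the baseline and endline surveys will take place during home visits conducted by qualified interviewers". A few days earlier, interviewer-pathfinder pairs visit the villages and households to explain the objectives, "inform subjects of their next interviews, and obtain the necessary prior approval".

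Section IV (Ethics) fixes the consent rule: "Consent will be obtained via the head of household (or their spouse, if absent". On risk it says that "the evaluation does not represent any risks to participants, as it consists simply of questionnaires administered by interviewers", and it adds the painless body measurements.

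The protocol also offers general protections. On administration, Section 3.2.4 says: "The questionnaire will be administered confidentially, ideally over a period of 90 to 120 minutes". Section IV adds that "any members of the household reserve the right to opt out of the survey without any negative consequences". It also lets a household or individual withdraw consent, postpone a visit or decline any item without giving a reason, and it promises confidentiality from data collection through to publication.

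**The concern.** The consent rule was written for a household survey, but it also governs a module on abuse within that household. Where the head is the woman's partner and is at home, permission comes from the person the questions may be about. The woman's position is then that she may decline something already agreed on her behalf. The risk statement rests on the study being nothing more than questionnaires and measurements, and that reasoning overlooks what one of the questionnaires asks. An ethics committee reading the risk entry alone would see nothing to mitigate.

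Two things are at stake. The first is protection of the women interviewed. The second is how far the partner-violence answers can be trusted, since a woman who is unsure who can hear her, or who agreed to the questions, may not disclose.

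**Working it through.** The protocol gives no figure for partner violence (no prevalence, disclosure rate or target difference), so there is nothing to reproduce. The check is mainly of the text.

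**Setting the passages side by side**

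| Question | What the protocol provides | Where |
|---|---|---|
| Is abuse asked about and analysed? | Yes: mother's module and a pre-specified intermediate outcome | 3.2.5; 3.2.6 |
| Where is the interview? | At home, in both surveys | 3.2.4 |
| Who consents? | Head of household, or the head's spouse if the head is absent | IV |
| Does the woman consent herself? | Not described; she may opt out, revoke or refuse items | IV |
| Is she interviewed alone? | Not stated; administration is to be confidential | 3.2.4; IV |
| What risk is declared? | None | IV |
| What follows a problem found at a visit? | Medical care for emergencies and severe health problems; nothing on disclosed violence | IV |

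The risk entry cannot be reconciled with the first row, because its stated reason does not cover questions about abuse. The consent rule and the first row can coexist, but only by leaving the woman's own agreement implicit.

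**Effect of under-reporting on the estimate (assumed values)**

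Let *s* be the probability that a woman who has experienced violence reports it, and assume no false reports. Reported prevalence is then *s* × true prevalence. If *s* is the same in both arms and both surveys, a risk-scale difference-in-differences is multiplied by *s*. For an assumed true value of 6 points:

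- *s* = 0.9: 0.9 × 6 = 5.4 points
- *s* = 0.7: 0.7 × 6 = 4.2 points
- *s* = 0.5: 0.5 × 6 = 3.0 points

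Section 3.2.6 plans logistic regression for binary variables, and on the odds-ratio scale the shrinkage is milder. Assume 30% in both arms at baseline, 30% in control at endline and 24% in intervention at endline. The baseline odds ratio is 1, so the interaction equals the endline odds ratio:

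- Full disclosure: (0.24 × 0.70) / (0.30 × 0.76) = 0.168 / 0.228 = 0.74
- *s* = 0.7 (reported 16.8% and 21%): (0.168 × 0.79) / (0.21 × 0.832) = 0.13272 / 0.17472 = 0.76
- *s* = 0.5 (reported 12% and 15%): (0.12 × 0.85) / (0.15 × 0.88) = 0.102 / 0.132 = 0.77

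In these examples equal under-reporting pulls the estimate toward no effect and does not create one. A false effect needs disclosure to change differently by arm. If *s* differs between arms by *d* at endline only, the spurious risk-scale difference is *d* × true endline prevalence. The protocol supplies neither quantity, so no size is given here.

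**The case against.** The best defence is that the protocol protects the woman more than the consent sentence suggests. She may refuse any item, which bears directly on these questions. An individual may revoke consent, which arguably treats her as having given it. Information goes to participating individuals as well as households and is explained in a language they understand. Confidentiality is promised from data collection onward. Private-interview procedure often sits in a field manual, which is not shown, and the protocol goes to national ethics review. All of this stands and lowers the severity. It does not close the gap: a right to refuse after someone else has agreed is not consent, confidential is not defined as alone, and a field manual would leave the consent rule and the risk sentence as written.

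Four stronger readings are tempting but unsupported:

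- A reader might infer that the partner is told about the violence questions. The advance information covers the study's objectives and implementation, and the objectives in the Introduction and Section 3.1 do not name partner violence.
- A reader might infer that the effect estimate is biased by arm. The consent rule is identical in both arms and both surveys. A differential would have to come from something else, such as cash changing household relations in intervention villages. That is possible, but the consent rule does not create it and its direction is unknown.
- A reader might turn the 1,020 per group in Section 3.2.3 into a count of women exposed. That figure is for children at baseline, and no endline number is given.
- A reader might think the trial's main result is threatened. HAZ, stunting and WHZ do not depend on these answers.

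**Conclusion.** The point holds as one of consent, privacy and an incorrect risk statement. The protocol asks mothers at home about abuse, pre-specifies partner violence as an outcome, takes consent via someone who may be the partner concerned, and declares no risk for a reason that does not cover those questions. The general safeguards reduce the problem without removing it.

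For the estimate, under-reporting is a reasonable inference, not something the protocol states. If it is equal across arms and surveys it weakens the partner-violence effect; the sizes shown rest on assumed disclosure of 50% to 90%, an assumed 6-point effect and, for the odds ratios, an assumed 30% prevalence. Bias between arms remains possible and unquantified. The consequence is confined to one intermediate outcome. On validity grounds this is not a must-fix; the case for changing it rests mainly on protecting participants, and the change is cheap.

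**What to change.** 1. Keep the head of household's permission for the household survey. Add the mother's own consent, taken in private, for the module on women's status and partner violence.
2. State in Section 3.2.4 that she is interviewed alone for this module and that the module stops if privacy is lost.
3. Describe the module to other household members only in general terms.
4. Replace the risk sentence in Section IV with one that acknowledges the sensitivity of these questions and is consistent with Sections 3.2.5 and 3.2.6.
5. Record module completion and report it by arm, so that a difference in non-response can be seen.

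The cost is revised consent wording and some interviewer training; the interviewers and the questionnaire stay the same. The downside is some missing partner-violence modules where privacy cannot be obtained, which is why completion should be reported by arm.
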